### Study outcomes

The primary outcome measures being assessed between the intervention and control facilities are: i) proportion of screened individuals for hypertension, ii) newly diagnosed patients with hypertension or CVD, iii) prescription of guideline directed medical therapy for hypertension and CVD, iv) BP control defined as < 140/90 mmHg, v) provider knowledge and practice related to hypertension and CVD and vi) patient centered care and satisfaction. The study also assesses several secondary outcome measures including difference in total waiting time for physician consultation and physician acceptability of the GHI.

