### Statistical analysis

Quantitative data is analyzed by descriptive statistics for demographic, socio-economic and other patient-, provider- and health system level factors between the intervention and control facilities. Differences in service delivery indicators, process of care measures (prescription of guideline directed medical therapy) and clinical outcomes (BP control) will be compared between the intervention and control facilities. The chi-square test is used to evaluate differences between categorical variables. Two-sided p-values < 0.05 will be considered statistically significant. Composite performance scores are defined by determining the proportion of patients who receive concordant care compared to patients who receive discordant care between the intervention and control facilities. Linear and logistic regression analysis techniques are used to assess determinants of health outcomes, processes of care measures, and treatment satisfaction [33]. Random-effects regression analyses will be used to account for cluster effects and imbalances between intervention and control group health facilities; Effect sizes will be presented as risk ratios for binary outcomes, and as mean differences for continuous outcomes; 95% confidence intervals (CI) will be given for both. Missing data in outcome measures will be handled by appropriate imputation methods.

A propensity score will also be created using logistic regression and will contain those variables associated with treatment at a health facility [34]. Analysis of clinical outcomes analysis will also use ANCOVA (analysis of covariance) to compare the prescription of evidence-based medicines, and mean change in BP and lipids between the intervention and control arm facilities [29]. Other outcome measures such as behavioural and biochemical risk factors will be analyzed using logistic or conditional logistic regression to adjust the comparisons for other variables. We shall also compare the percentages achieving clinical and behavioural targets between the intervention and control arm facilities.

The fidelity analysis will uncover the extent to which the GHI was fully or partially implemented by various health system stakeholders.

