Next, when analyzing the KAP survey we will report the demographic characteristics of healthcare providers by the intervention and control arm facilities, reporting the mean (standard deviations, SD) or median (25th and 75th percentiles) for continuous variables and frequencies (percentages) for categorical variables. Knowledge about CVD symptoms and modifiable risk factors will be reported as number (percent) by overall and intervention and control arm facilities. Next, each correct response for knowledge related questions will be assigned a score of 1 and the total score for the knowledge of CVD risk factors and treatment recommendations will divided by tertiles and classified as minimal, moderate, and high knowledge. The mean (SD) for knowledge of CVD risk factors and treatment will also be reported by intervention and control facilities. Finally, the correct scores for the knowledge of CVD risk factors and treatment strategies will be classified into high knowledge (> 75% correct responses) and poor knowledge (≤ 75% correct responses) using arbitrary threshold for comparison and also informed by the published literature [35] [36]. The chi-square test will be performed to investigate the difference in knowledge scores between intervention and control arm facilities across age-group, sex, and education strata. Bivariable and multivariable regression analyses will be performed to assess the factors associated with high knowledge of CVD symptoms, and modifiable risk factors. The unadjusted and adjusted odds ratio with 95% confidence intervals (CI) will be reported. The model will be adjusted for age, sex, type of health facility and type of healthcare worker.

Lastly, an interrupted time-series analyses (ITSA) is carried out to establish effects of the GHI on the screening, diagnosis, and management of hypertension / CVD, if aggregate facility-level monthly data are available from the DHIMS2. ITSAs apply segmented regression to assess the impact of events that have occurred at a clearly defined point in time. Data points recorded in the GHI enabled DHIMS2 system will be analyzed by month to examine trends over time and seasonality. We will also evaluate change in patient outcomes over time (e.g., mean systolic BP change).

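### Provider knowledge is scored on a full scale, but the only between-arm test and the only regression named for it use categorised versions of that score

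*Protocol article*

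**What the plan says.** Study outcomes lists "v) provider knowledge and practice related to hypertension and CVD" among the primary outcome measures.

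The knowledge-survey paragraph under Statistical analysis first builds a numerical measure: "each correct response for knowledge related questions will be assigned a score of 1 and the total score for the knowledge" is formed by summing. It then treats that score in three ways:

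- It is divided into tertiles labelled minimal, moderate and high.
- It is summarised uncut: "The mean (SD) for knowledge of CVD risk factors and treatment will also be reported by intervention and control facilities". No test, effect estimate or interval is attached.
- It is split at 75% correct, the lower class being "poor knowledge (≤ 75% correct responses) using arbitrary threshold for comparison and also informed by the published literature".

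For comparing arms the paragraph says: "The chi-square test will be performed to investigate the difference in knowledge scores between intervention and control arm facilities", within age, sex and education strata. Its regressions model high knowledge and report odds ratios. The listed adjustment variables are age, sex, facility type and staff category; study arm is not among them.

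The general part of the same section says: "Effect sizes will be presented as risk ratios for binary outcomes, and as mean differences for continuous outcomes", each with a 95% CI, and plans random-effects regression for clustering. The knowledge paragraph does not refer back to either.

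**The concern.** A chi-square test needs categories, and odds ratios for high knowledge need a two-way split. The methods named for this outcome therefore use a coarser measure than the one the plan has already computed. Under a 75% cut, a provider who moves from 50% to 70% correct counts as unchanged, while one who moves from 75% to 80% counts as a full success. The result then depends partly on where the control average lies relative to a line that the protocol itself calls arbitrary.

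Health-worker training is one of the programme's five components, so knowledge is where an effect should show first. The survey takes the eligible providers present on the visit day at 98 facilities (42 + 56), so power lost in the analysis is hard to recover by recruiting more.

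**Working it through.** **Inputs from the document.** 42 intervention and 56 control facilities; two-sided 0.05; cut at more than 75% correct; one point per correct answer. The Sample size section (1,200 participants, 90% power) covers only the record review or patient exit survey. There is no stated figure for the provider survey to reproduce.

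**Inputs assumed.** Providers per facility, number of items, SD, ICC, expected gain and control mean. None is given, so each is varied or labelled below.

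**Step 1: efficiency of a cut.** For a normal score and a small shift, the efficiency of a two-way split relative to the full score is φ(z)² / [F(1 − F)], where F is the share below the cut, z the matching normal quantile and φ the normal density.

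- 50/50 split: 0.399² / 0.25 = 0.64
- 80/20 split: 0.280² / 0.16 = 0.49
- 90/10 split: 0.1755² / 0.09 = 0.34

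This step needs no sample size. Even at the most favourable cut, about a third of the information is lost.

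**Step 2: power without clustering.** Take a standardised difference d = 0.3 and 175 providers per arm.

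- Full score: Φ(0.3 × √(175/2) − 1.96) = Φ(2.81 − 1.96) = 0.80.
- Cut score with 20% of controls above the line: z = 0.842, so the intervention share is 1 − Φ(0.842 − 0.3) = 0.294. The pooled standard error is √(2 × 0.247 × 0.753 / 175) = 0.0461 and the unpooled one 0.0458. Power is Φ[(0.094 − 1.96 × 0.0461) / 0.0458] = Φ(0.08) = 0.53.

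With 50%, 30% or 10% of controls above the line, cut-score power is 0.60, 0.585 or 0.42. Simulated bounded scores of 10, 20 or 30 items at similar inputs lost about 14 to 40 points, so the direction does not depend on exact normality.

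**Step 3: power with clustering.** Simulation with 4,000 replicates per setting: 42 versus 56 facilities, a 20-item score, SD 15 percentage points, a facility random effect, and a two-sided t-test on facility means (full score) or on facility proportions above 75% (cut). Where not stated, ranges cover control means 60, 70 and 75 and ICC 0.05 to 0.10.

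| Providers per facility | Gain (points) | Setting | Full | Cut | Loss (points) |
|---|---|---|---|---|---|
| 5 | 2 | range | 0.23–0.25 | – | 5–11 |
| 5 | 4 | mean 60, ICC 0.05 | 0.74 | 0.45 | 29 |
| 5 | 5 | mean 60, ICC 0.05 | 0.91 | 0.65 | 26 |
| 5 | 5 | mean 75, ICC 0.10 | 0.85 | 0.72 | 13 |
| 5 | 8 | range | 0.99–1.00 | 0.96–0.99 | 1–4 |
| 10 | 4 | range, ICC 0.10 | – | – | 9–21 |
| 10 | 5 | range | – | – | 4–15 |
| 15 | 4 | range, ICC 0.10 | – | – | 7–16 |
| 15 | 5 | range | – | – | 1–8 |

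With no true difference, both tests rejected about 5% of the time (0.044 to 0.056), so the comparison of power is fair. The Monte Carlo standard error of one power estimate is at most √(0.25/4,000) = 0.008. Allowing for that, the full score was never worse.

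**The case against.** Four points can be made for the plan.

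- **The general rule already covers it.** The section promises differences in means with intervals for continuous outcomes and random-effects models, and the knowledge paragraph reports the mean score by arm. A reader could put these together. That stands as far as it goes: the uncut score is neither discarded nor excluded. But the paragraph specific to this outcome names other methods and attaches no comparison to the mean.
- **The cut is not declared primary.** The chi-square sentence concerns strata and the regression concerns determinants of high knowledge. A reader might infer that the 75% class carries the primary comparison. The document does not say so, and a full protocol or SAP may settle it. What remains is that the methods the article does name for this outcome are categorical ones.
- **The cut is fixed in advance and also said to rest on literature.** Both are true. A reader who stops at the word arbitrary might suspect a data-driven threshold, and the text does not support that. Fixing a cut in advance prevents choosing it from the results, but it does not restore the information lost.
- **The loss may be negligible.** Visits cover sites up to tertiary level, so more than five providers per facility is plausible, and training with coaching could yield a gain of about half an SD (8/15 = 0.53). At a gain of 8 points with five providers per facility, the loss is only 1 to 4 points. This stands, and it rules out quoting a single figure.

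**Conclusion.** The point holds as a modest, inexpensive improvement. The loss of efficiency is general: the 64% ceiling for a two-way split needs only an approximately normal score and a small shift. The loss of power is conditional on the assumed inputs and is largest in the table at a gain of 4 points, control mean 60 and five providers per facility. A reader might take one band of lost power as a property of this study, or conclude that a real gain would probably be reported as no effect. The document supports neither, because it gives none of the inputs needed. The point concerns only how knowledge is measured in the comparison; it would remain with a single cut, correct clustering and an arm term in the model.

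**What to change.** In the knowledge-survey paragraph, state that the main between-arm analysis of provider knowledge is the difference in mean percent-correct score with its 95% CI. Estimate it by the random-effects linear regression the section already plans, with study arm as the term of interest, a random effect for facility, and the covariates already listed (age, sex, facility type, staff category). Label the tertiles and the 75% class as descriptive or supportive.

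The cost is a sentence or two of text. The score is computed in any case, and no further data are needed. The one drawback is that a difference in points is less immediate to readers than a percentage with high knowledge; the retained summary covers that and keeps any comparison with published work.

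### For provider knowledge, a primary outcome, the only named arm test is an unclustered chi-square, and the planned random-effects comparison is not carried into that analysis

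*Protocol article*

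**What the plan says.** All references are to the protocol article.

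- **Status of the outcome.** Study outcomes lists "v) provider knowledge and practice related to hypertension and CVD" among the primary outcome measures.
- **Sampling.** Under Quantitative study component, every eligible provider who is present and available on the visit day is interviewed. The Abstract gives 42 intervention and 56 control facilities.
- **General rules (Statistical analysis, first paragraph).** "The chi-square test is used to evaluate differences between categorical variables", with significance at a two-sided p below 0.05. The same paragraph plans random-effects regression for cluster effects and for imbalance between the two groups of facilities, and it limits this to no particular outcome. It adds: "Effect sizes will be presented as risk ratios for binary outcomes", with mean differences for continuous outcomes.
- **Provider survey (Statistical analysis, paragraph on the knowledge, attitudes and practices survey).** The between-arm test is "The chi-square test will be performed to investigate the difference in knowledge scores between intervention and control arm facilities", across strata of age group, sex and education. A bivariable and multivariable regression then looks for factors associated with high knowledge. For it, "The model will be adjusted for age, sex, type of health facility and type of healthcare worker" and "The unadjusted and adjusted odds ratio with 95% confidence intervals (CI) will be reported".
- **Two uses of one label.** The total score "will divided by tertiles and classified as minimal, moderate, and high knowledge". Later in the paragraph the scores are split into "high knowledge (> 75% correct responses) and poor knowledge".

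**The concern.** Providers in one facility share training, equipment, guidelines and supervision, so their knowledge scores are likely to be correlated. An ordinary chi-square treats each provider as independent. When the treatment varies only between facilities, that understates the variance of the arm difference, and p-values come out too small.

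The survey paragraph offers nothing better for the arm question. Its test is run within strata, so it yields several p-values and no stated overall effect, and it does not adjust for worker type or facility type. Facilities were not randomised, and the limitations under Evaluation Design Strengths and Weaknesses warn of imbalance in provider education, training and experience and promise adjusted analyses. The regression in the survey paragraph does adjust, but its stated aim is to find who scores well, and arm is not named in it.

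An analyst who follows the survey paragraph as written would therefore judge a primary outcome by an anti-conservative, unadjusted test. One who follows the general paragraph would use a clustered model and a different effect measure. The article does not say which prevails.

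**Working it through.** **1. The two sets of instructions for the same outcome**

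| Item | General paragraph | Provider-survey paragraph |
|---|---|---|
| Arm comparison | Chi-square for categorical variables; random-effects regression for cluster effects and imbalance | Chi-square within age, sex and education strata |
| Facility effect | Yes, in the regression | Not mentioned |
| Arm as a model term | Implied by the comparison of the two groups | Not listed |
| Effect measure | Risk ratio or mean difference | Odds ratio |
| Outcome | Not specific to knowledge | Mean score, tertile class, and above 75% correct |

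The score described covers risk factors and treatment, whereas the regression outcome is worded as symptoms and modifiable risk factors. Education is a stratum variable for the chi-square but is not among the listed model covariates.

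**2. Inputs for the size of the error**

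- Alpha: two-sided 0.05 (Statistical analysis).
- Facilities: 42 and 56 (Abstract).
- Providers per facility, *m*: not given, so assumed at 3, 5, 10 and 20.
- ICC: not given, so assumed at 0.01, 0.05, 0.10 and 0.20.

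The article has no provider sample size to reproduce. The 1,200 under Sample size is for the medical record review or the patient exit survey, so it should not be used to derive *m* here.

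**3. Formulas**

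Design effect: DE = 1 + (*m* − 1) × ICC.

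Actual type I error of a test that ignores clustering: 2 × [1 − Φ(1.96/√DE)].

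**4. Worked cases**

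- *m* = 3, ICC 0.01: DE = 1 + 2 × 0.01 = 1.02; type I error 0.052.
- *m* = 3, ICC 0.05: DE = 1 + 2 × 0.05 = 1.10; type I error 0.062.
- *m* = 10, ICC 0.05: DE = 1 + 9 × 0.05 = 1.45; type I error 0.104.
- *m* = 20, ICC 0.10: DE = 1 + 19 × 0.10 = 2.90; type I error 0.250.

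Full grid of actual type I error at nominal 0.05:

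| *m* | ICC 0.01 | ICC 0.05 | ICC 0.10 | ICC 0.20 |
|---|---|---|---|---|
| 3 | 0.052 | 0.062 | 0.074 | 0.098 |
| 5 | 0.055 | 0.074 | 0.098 | 0.144 |
| 10 | 0.060 | 0.104 | 0.155 | 0.241 |
| 20 | 0.072 | 0.160 | 0.250 | 0.371 |

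A beta-binomial simulation of 42 against 56 facilities agrees. It gives 0.073 and 0.095 for *m* = 5 at ICC 0.05 and 0.10, and 0.100 and 0.155 for *m* = 10 at the same ICCs.

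**5. Why the effect measure must be settled**

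The two measures are not interchangeable when the outcome is common. With assumed proportions of 55% against 50%, the risk ratio is 0.55/0.50 = 1.10 and the odds ratio is (0.55/0.45)/(0.50/0.50) = 1.22. With 88% against 80%, the risk ratio is again 1.10 and the odds ratio is (0.88/0.12)/(0.80/0.20) = 1.83.

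**The case against.** The strongest reply is that clustering is already planned. The random-effects sentence is not tied to any outcome, the survey paragraph belongs to the same section, and a condensed article need not repeat a general rule for each outcome. This stands in part. A reader might infer that the plan ignores clustering altogether and will yield no adjusted arm effect for knowledge. The article does not support that: it plans a cluster-adjusted comparison in general terms, and for the survey regression it is silent on facility effects, not explicitly unclustered. What remains is that the survey paragraph sets out its own test and effect measure, and that the test it names is unclustered.

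A reader might also infer that the survey regression has no arm term. That too goes beyond the text. The list gives adjustment covariates, and such lists often leave out the exposure of interest. Arm could be one of the unnamed factors. The supportable statement is that arm is not listed.

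On the two classifications, tertiles give three levels and only the 75% cut is binary, so odds ratios for high knowledge fit that cut most naturally. The overlap is largely one of labelling, though the regression does not say which it means. An odds ratio from a determinants model, reported as such, is not in itself an error.

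Finally, the inflation depends on cluster size. With few providers per facility, and fewer still within strata, it can be small. That is correct, and it is why the size is given as a range.

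**Conclusion.** The point holds as an unresolved conflict within Statistical analysis for a primary outcome, together with a named test that is wrong for arm inference. If the chi-square p-values are used to compare arms, they are too small whenever the ICC is above zero and facilities contribute more than one provider each.

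The size rests on assumed values. It is negligible at 3 providers per facility and ICC 0.01 (about 5%) and modest at 3 and ICC 0.05 (about 6%). It doubles the nominal rate at 10 and ICC 0.05 (about 10%) and reaches five times the nominal rate at 20 and ICC 0.10 (about 25%). The article does not allow a choice among these. The same reasoning applies to the categorical arm comparisons in the general paragraph, where respondents are also grouped by facility.

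**What to change.** 1. Keep chi-square for description only, without p-values for arm effects, both in the provider-survey paragraph and for the categorical arm comparisons in the general paragraph.
2. State that the arm comparison of knowledge uses the random-effects model already planned, with a facility random effect, arm as the term of interest, and adjustment for facility type, worker type, age and sex.
3. Report a mean difference in total score and, for one binary definition (above 75% correct), a risk ratio, each with a 95% confidence interval, as the general paragraph promises.
4. Reserve the label high knowledge for that binary definition. Whether the tertile classes stay as description, and which method is used to obtain the risk ratio, are matters of preference.

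The change is to analysis wording alone and needs no new data. The price is wider intervals and less favourable p-values than the unclustered tests would give.

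### For provider knowledge, a primary outcome, the KAP paragraph's only named between-arm test is a chi-square across strata; it names no overall arm test and no interaction, and does not refer to the clustered model

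*Protocol article*

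**What the plan says.** Study outcomes lists "provider knowledge and practice related to hypertension and CVD" as the fifth of six primary outcome measures. The analysis of knowledge is set out in the KAP paragraph of Statistical analysis:

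- Overall knowledge by arm is described, not tested: "The mean (SD) for knowledge of CVD risk factors and treatment will also be reported by intervention and control facilities". Counts and percentages by arm are also reported.
- The score is cut into tertiles, and separately at 75% correct, to define high and poor knowledge.
- The one between-arm test named is: "The chi-square test will be performed to investigate the difference in knowledge scores between intervention and control arm facilities across age-group, sex, and education strata".
- A regression follows: "Bivariable and multivariable regression analyses will be performed to assess the factors associated with high knowledge of CVD symptoms, and modifiable risk factors". On its covariates the text says: "The model will be adjusted for age, sex, type of health facility and type of healthcare worker". Study arm is not listed, nor is any product of arm with another factor. Results are to be odds ratios.

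The general part of the same section sets the significance rule, "Two-sided p-values < 0.05 will be considered statistically significant", and adds: "Random-effects regression analyses will be used to account for cluster effects and imbalances between intervention and control group health facilities". Effects there are risk ratios or mean differences with 95% confidence intervals. The KAP paragraph does not refer to this model, and it reports odds ratios where the general part specifies risk ratios for binary outcomes.

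**The concern.** The natural reading of the chi-square sentence is an arm comparison repeated within each age, sex and education stratum. That answers neither question a reader would have.

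- **Does the programme raise knowledge?** Each stratum test uses only part of the sample, so it has less power than a single overall comparison. Several tests at 0.05 also leave it open which one decides the outcome.
- **Does the effect differ between kinds of provider?** A significant stratum beside a non-significant one is not evidence of a difference. That needs a test of the arm-by-stratum interaction.

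A plain chi-square also treats providers in the same facility as independent. Training of health workers is one of the five programme components, and the evaluation is meant to inform national scale-up. A misread pattern across strata could therefore influence who is trained.

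**Working it through.** **Inputs from the article.** Two-sided 0.05 for each test; strata by age group, sex and education; 42 intervention and 56 control facilities, so 98 in all.

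**Inputs not in the article, hence assumed.** The number of strata (6 to 12), the number of providers, the share with high knowledge, the overall power and the intraclass correlation (ICC). The article gives no figure for this analysis, so there is nothing to reproduce. Its 90% power and 1,200 participants belong to the medical record review or patient exit survey, not to the provider survey.

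**1. No true effect.** If the k strata were independent, the chance of at least one p < 0.05 would be 1 − 0.95^k. The same providers appear in the age, sex and education strata, so the tests overlap and the true figure is lower. A simulation with 600 providers, equal arms, 50% high knowledge and no clustering gives the third column.

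| Strata k | Independent, 1 − 0.95^k | Overlapping, simulated | Expected number significant, 0.05k |
|---|---|---|---|
| 6 | 26.5% | 20.5% | 0.3 |
| 8 | 33.7% | 29.5% | 0.4 |
| 10 | 40.1% | 35.3% | 0.5 |
| 12 | 46.0% | 41.7% | 0.6 |

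A second simulation for 8 strata, with 800 providers and 40% high knowledge, gives 28.7%. About 29% is therefore stable over these two sets of inputs.

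**2. The same true effect in every stratum.** Assume 90% power for one overall test. The standardised effect is then 1.960 + 1.282 = 3.24.

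- Two equal strata: 3.24/√2 = 2.29, so power in each is Φ(2.29 − 1.96) ≈ 0.63. Exactly one is significant with probability 2 × 0.63 × 0.37 = 0.47.
- Three equal strata: 3.24/√3 = 1.87, so power in each is Φ(1.87 − 1.96) ≈ 0.465. Results are mixed with probability 1 − 0.465³ − 0.535³ = 0.75.
- Eight overlapping strata, simulated with 600 providers and a uniform 15-point effect on a 50% baseline: one overall test is significant in 97% of studies, yet 88% of studies show a mix of significant and non-significant strata.

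In all three cases there is no heterogeneity to find.

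**3. Clustering.** Assume 6 providers per facility and 100 facilities, close to the actual 98. With 8 strata and no effect, the chance of at least one significant stratum rises to 32% at an ICC of 0.05 and 34% at 0.10. A single overall chi-square that ignores clustering then has a type I error of about 9% and 11% instead of 5%. Replacing the stratum tests with one plain chi-square would therefore not be enough.

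**4. After the change.** One overall test from a model that allows for clustering is held at a nominal 5%. Three interaction tests at 0.05 give a chance of a false subgroup signal of about 1 − 0.95³ = 14.3% if treated as independent. Testing each at 0.05/3 = 0.0167 brings this to at most 5%.

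**The case against.** The strongest reply is that the general part of Statistical analysis already supplies a between-arm comparison. Its random-effects regression is not limited to patient outcomes, and both the knowledge score (a mean difference) and high versus poor knowledge (a risk ratio) fit it. This stands. A reader might infer that the stratum chi-square is the only between-arm test the plan allows for knowledge. The article does not support that; it is only the one named in the KAP paragraph.

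Two further inferences also go too far. A reader might conclude that chance will produce significant strata. Under the assumptions above it does so in about 21% to 42% of studies, with fewer than one such stratum expected. A reader might also conclude that the plan sets out to claim who benefits. It announces no subgroup hypothesis and no decision based on strata, so misreading is a risk and not a stated intention.

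The sentence is also condensed. The word across could mean a pooled stratified comparison or a descriptive breakdown, though separate tests are the more natural reading. All the sizes depend on assumed inputs.

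It can also be said that interaction terms and multiplicity belong in an analysis plan that is not shown. That would answer a complaint about missing detail. Here, however, the article states a method for a primary outcome, and that method cannot answer whether effects differ. Nor does the KAP paragraph say that the general clustered model decides the outcome.

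**Conclusion.** The point holds in this form: the KAP paragraph fixes a stratum-wise chi-square as its only named between-arm test of a primary outcome. It names no overall arm test, arm term or interaction, and no link to the facility-clustered model elsewhere in the section. Stratum tests are inefficient for the overall effect, ignore clustering and cannot show that effects differ.

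On assumed inputs, the chance of at least one significant stratum with no effect is about 21% to 42% for 6 to 12 overlapping strata. With a uniform effect and 90% overall power, a split result in two equal strata occurs about 47% of the time. The reasoning does not depend on these inputs; the sizes do. The plan should be changed, but the defect lies in how the analysis is specified and does not affect the data collected.

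**What to change.** In the KAP paragraph:

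1. Name one overall arm comparison of the knowledge score as the main analysis, using the section's random-effects model with facility as the cluster, and report the mean difference with its 95% confidence interval.
2. Delete the chi-square tests by stratum. Add arm-by-age, arm-by-sex and arm-by-education terms to that model. Education must then enter as a main effect too, since the KAP regression's adjustment set does not list it.
3. Label the interactions exploratory, or test each at 0.05/3.
4. Show stratum estimates with 95% confidence intervals and no p-values within strata.

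The cost is a change of wording. Arm, age, sex and education are already needed for the planned analysis, so nothing new is collected. The downside is that interaction tests have low power, so fewer statements about subgroups will be possible.
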